#### Additional analyses

To assess overall recovery, mean and Standard Deviation (SD) of the functional outcome scores are calculated using the paired T-test. In case of skewed data the Wilcoxon signed rank test will be used instead, reporting the median and range.

To assess whether the received treatment affects functional outcome and/or the progression to CAI will be assessed. Depending on normality of data the Pearson’s or Spearman’s rho will be used.

Finally based on the amount of ankle sprains experienced prior to participation in this study, patients will be defined as suffering from an acute lateral ankle sprain (LAS) or CAI. The correlation coefficient of acute LAS and bone geometric factors, and CAI and bone geometric factors will be calculated using the Pearson’s or Spearman’s rho (depending on normality or skewed data). These correlation coefficients will be compared to see whether there is a difference in bone geometry between acute LAS or CAI patients.

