**Methods:**

In this observational prospective cohort, all patients aged sixteen years and older, reporting at the emergency department of one of the participating hospitals after sustaining a lateral ankle sprain, and filled out 1 out of 3 follow-up questionnaires and the 1 year follow-up are included. A lateral and anteroposterior radiograph is made. Patients are excluded if a fracture or other pathology is present. The included patients receive four questionnaires, including questions focusing on the sprain, treatment and complaints, the Foot and Ankle Outcome Score and the Cumberland Ankle Instability Tool. A total of eleven radiographic variables are assessed for inter- and intra-observer reliability. Additionally, four factors extracted from the questionnaires, will be evaluated for correlation with CAI. Significantly correlating factors (e.a. risk factors) will be implemented in a risk assessment model. For the final model, based on sixteen variables with a minimum of 20 events per variable and a prevalence of 30–40% after an initial sprain, a sample size of 2370 patients is needed to perform both internal and external model validation.

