### Study centres and participants

This study will be conducted at the ER of four Dutch hospitals: the AMC Amsterdam, Flevoziekenhuis Almere, Slotervaart Medical Center Amsterdam, VUmc Amsterdam. All subsequent patients that present themselves at the ER of one of the participating hospitals after an initial lateral ankle sprain will be treated according to standard protocol, including anamnesis, physical examination and (in case of positive Ottawa Ankle Rules (OAR)*) a radiograph [24]. When a mortise view and lateral radiograph is made and negative for ankle fractures or other joint pathology, patients are screened for eligibility according to the in -and exclusion criteria (Table 1).

**Table 1 Tab1:** Inclusion- and exclusion criteria

Inclusion criteria	Exclusion criteria
At least 16 years old	Present fracture or other joint pathology/bone matrix pathology
Visited the ER within one week after a lateral ankle sprain	A diagnosed OCD after primary inclusion
Agreed with being approached for this study	Medial ankle instability
Reported anterolateral ankle pain after an ankle sprain or ankle distortion	Previous ankle surgery
Filled out the baseline, 3-, or 6 month questionnaire; and the 12 month follow-up	An unreliable radiograph due to the angle in which it is made or low quality
	Acute surgical repair or the ATFL/CFL or any other form of surgery within 12 months after the ER visit

*Abbreviations*: *ER* Emergency Department, *AP* anteroposterior, *OCD* osteochondral defect, *ATFL* anterior talofibular ligament, *CFL* calcaneofibular ligament

*The OAR are a requirement at the ER according to Dutch protocols to conclude whether there is an indication for a radiograph. However, in cases of severe LAS patients there is a high risk at false positive OAR despite the absence of a fracture (due to a painful lateral malleolus with or without the ability to bear weight).

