#### Follow-up

A legally required waiting period of two weeks is observed prior to asking consent and sending the questionnaires to the patient’s home address or email address. Patients are asked to fill out the first questionnaire immediately which gives a T0 (baseline measure at approximately two weeks after the initial sprain). The subsequent evaluation time points are T1 interim evaluation after three months, T2 after six months, and T3 at twelve months. The questionnaires contain questions about patient characteristics, previous ankle sprains, treatment, restrictions and complaints. Additionally the questionnaires contains the Foot and Ankle Outcome Score (FAOS) and the Cumberland Ankle Instability Tool (CAIT) to evaluate recovery. To ensure all patients with CAI are identified, one year after their ER visit they will be contacted, inquiring on persisting complaints and ankle instability. Patients that indicate on the first questionnaire they sustained ankle sprains prior to their ER visit will not receive further follow-up questionnaires, as these patients are considered to have CAI and therefore need no extra monitoring to identify whether they develop CAI or not. They will not be included in the primary analysis as this may lead to overfitting of the current model. Concomitant neuromuscular adaptations and additionally may follow a different rehabilitation route due to familiarity with the complaints.

In case of persisting complaints six months after the ER visit, patients will be eligible for surgical treatment according to Dutch standards. This is to avoid unnecessary invasive treatment on patients as a large proportion recover by means of conservative treatment [7].

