#### Additional analyses

By comparing PROM scores over time, overall recovery will be assessed. In addition, the different treatments and symptoms during physical examination will be assessed for their relation to the functional outcome, as measured by the FAOS and CAIT and persisting complaints of instability. The final sub-analysis differentiates between the amount of recurrent ankle sprains prior to the initial ER visit to check whether the model is also applicable on patients that already suffer from CAI, as identified by the first questionnaire.

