## Abbreviations

AAI: Ankle activity index
AMC: Academic Medical Center
BMI: Body Mass Index
CAI: Chronic ankle instability
CAIT: Cumberland ankle instability tool
EPV: Events per variable
ER: Emergency department
FAOS: Foot and ankle outcome score
ICC: Intraclass correlation coefficient
IRB: Institutional review board
LAS: Lateral ankle sprain
MDTA: Medial distal tibial angle
MM: Millimeters
OAR: Ottawa ankle rules
PROM: Patient reported outcome measure
SD: Standard deviation
SDC: Smallest detectable change
SEM: Smallest detectable change
T0: First questionnaire two weeks after consent is received
T1: Second questionnaire after 3 months
T2: Third questionnaire after 6 months
VUmc: VU Medisch Centrum

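### Paired tests of FAOS/CAIT recovery sit badly with an inclusion rule that needs only one early questionnaire: each comparison uses a different subset, and changes involving the 3- or 6-month form may be biased

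*Protocol article*

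**What the plan says.** The aim is given under Analyses, Additional analyses: "By comparing PROM scores over time, overall recovery will be assessed". The method follows under Data analysis and statistics, Additional analyses: "To assess overall recovery, mean and Standard Deviation (SD) of the functional outcome scores are calculated using the paired T-test", and "In case of skewed data the Wilcoxon signed rank test will be used instead, reporting the median and range". Which time points are to be paired is not stated.

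FAOS and CAIT are on questionnaires sent at T0 and at three later points (Follow-up): "The subsequent evaluation time points are T1 interim evaluation after three months, T2 after six months, and T3 at twelve months". Table 1 sets the form requirement for inclusion: "Filled out the baseline, 3-, or 6 month questionnaire; and the 12 month follow-up". The abstract's Methods say the same: "filled out 1 out of 3 follow-up questionnaires and the 1 year follow-up are included". Study design confirms that only the 12-month form is mandatory.

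The Missing data section deals with a missing 12-month outcome and a missing radiograph. It gives no rule for a missing T0, 3- or 6-month score.

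T0 is defined twice. Follow-up describes the first questionnaire as one "which gives a T0 (baseline measure at approximately two weeks after the initial sprain"), and Study design also gives 2 weeks after the sprain. The abbreviation list reads: "T0: First questionnaire two weeks after consent is received".

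**The concern.** The inclusion rule accepts incomplete early data by design, while the named tests can use only patients with both members of a pair. If T0-T1, T1-T2, T2-T3 and T0-T3 are each tested, each is estimated in a different set of patients, and the steps need not add up to the whole.

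The pairs may also be selected. Suppose patients with worse scores at one visit are more likely to return the next form. The pairs then over-represent low starting scores, which tend to rise by regression to the mean, and the change looks too large. If better scorers return more often, it looks too small. At stake is the published account of how much function returns by 3, 6 and 12 months.

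**Working it through.** **The plan's own figures.** The article gives no sample size or response rate for the recovery analysis. Its model sample size does reproduce: 20 events × 16 coefficients = 320 events; 320 / 0.30 = 1066.7; 1066.7 / 0.9 = 1185.2, against 1185 stated. The 1067 patients before inflation for loss are used below only to turn shares into counts.

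**Step 1: who contributes to each pair.** From the plan: at least one of three early forms, and the 12-month form always present. Assumed: each early form is returned independently with probability r. The share with at least one early form is c = 1 − (1 − r)³. Among included patients:

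- early form paired with 12 months: r / c
- two early forms paired: r² / c
- all four forms: r³ / c

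| r | early vs 12 months | two early forms | all four |
|---|---|---|---|
| 0.5 | 57% | 29% | 14% |
| 0.6 | 64% | 38% | 23% |
| 0.7 | 72% | 50% | 35% |
| 0.8 | 81% | 65% | 52% |
| 0.9 | 90% | 81% | 73% |

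At r = 0.7, c = 1 − 0.027 = 0.973 and 0.49 / 0.973 = 0.504. Of 1067 patients, about 768, 537 and 376 contribute to the three columns.

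**Step 2: when the changes are biased.** For a pair T0-T1 with equal SDs and correlation ρ, if return of the T1 form depends only on the T0 score, the error in the mean change is (1 − ρ) × δ. Here δ is how far the mean T0 score of those who return T1 lies below that of all who returned T0. With δ = 0 there is no error, however many forms are missing.

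**Step 3: size under assumed mechanisms.** All inputs here are assumptions: normal scores, SD 20, true means 50/70/78/83, adjacent-visit correlation 0.4 or 0.6, T0 returned at random by 80%, T3 always present. Return of T1 and T2 depends on the last observed score, with log-odds 0.5 or 1.0 per SD (odds ratio e^0.5 = 1.6 to e^1.0 = 2.7).

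- Random return: no bias in any change.
- Worse scorers return more often: T0-T1 is too large by about 1.3 to 3.8 points, and T1-T2 by about 1.4 to 4.9 points (18% to 61% of the assumed true 8). The range covers repeated runs and different correlation patterns. By the formula in step 2, 3.7 points at ρ = 0.4 corresponds to δ = 3.7 / 0.6 = 6.2 points.
- The three paired steps then sum to about 2.7 to 9.7 points more than the paired T0-T3 change.
- The paired T0-T3 change itself is off by 0.1 points or less.
- Better scorers return more often: the signs reverse.
- A likelihood-based repeated-measures model on the same data is within 0.2 points.

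**Step 4: other mechanisms** (correlation 0.5).

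- Return of every early form, T0 included, depends on the score at that same visit or on the later improvement (means 50/65/75/80; odds ratios 0.8 to 0.4 per SD). Adjacent early steps are off by about 0. Early-to-12-month changes are off by about +0.7 to +2.6 points in the first case and −1.3 to −5.1 in the second.
- Return depends on an unobserved, stable severity that shifts all four scores equally. Paired changes are off by less than 0.1 points, while the model is off by about 0.5 to 1.7 points in some changes.

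**The case against.** Several points on the other side stand.

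- **A reader might infer that the reported recovery is biased.** The document does not support that. Different subsets alone do not bias a paired mean change, and the article gives neither a response rate per form nor any reason for non-response. Size and sign depend on the assumed mechanism.
- **The pairs are not named.** The adjacent early steps, where the larger errors in step 3 arise, are one reading. A T0-T3 contrast is at least as natural, and it holds up well if T0 return is unrelated to the scores.
- **The model can look better than it is.** Step 3 satisfies its assumptions by construction. A reader might infer that it always needs less than the paired tests do; the stable-severity scenario shows otherwise. Nor does it undo the restriction to 12-month responders.
- **A reader might link a distorted 3-to-6-month change to the six-month point for surgical eligibility.** The article takes that point from Dutch standards and cited work, not from this analysis.
- **A condensed article may leave intermittently missing secondary scores to a fuller plan.** That excuses the missing detail. It does not remove the mismatch, because the test and the inclusion rule are both stated here.
- **The T0 discrepancy has no bearing on paired versus mixed analysis.** The body text is consistent at about two weeks after the sprain; only the abbreviation list differs.

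**Conclusion.** The point holds in conditional form. With incomplete return, the paired tests use a different subset for each comparison and leave collected scores unused; that follows from the stated rules. Changes involving the 3- or 6-month form may be biased by a few points, in either direction, if return depends on earlier observed scores. There is no bias if non-response is random, and little in T0-T3 if T0 return is unrelated to the scores. Every point estimate above rests on assumed response rates, means, SD, correlations and mechanisms.

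The reach is limited to the additional recovery analysis. The risk model, the CAI outcome and the sample size do not use it. The T0 wording is a separate inconsistency: since consent is asked only after a two-week wait, the abbreviation list would put T0 at least about four weeks after the ER visit.

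**What to change.** - Make the main recovery analysis one linear mixed model for repeated measures per score (each FAOS subscale and CAIT), using all available T0-T3 scores, with time as a categorical effect and an unstructured covariance.
- Report model-based means and changes with 95% confidence intervals, and the number of patients contributing at each time point. If scores are skewed, use robust or bootstrap standard errors.
- Keep the paired t-test or Wilcoxon test as a sensitivity analysis, with the pairs named.
- Separately, reconcile the T0 entry in the abbreviation list with Study design and Follow-up.

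The cost is a change of wording and a little more analysis work, with no new data or patients. The downside is small: the model relies on missing at random, can be slightly off if unobserved stable severity drives return, and does not remove selection on 12-month response.

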**Fig. 6 Fig6:**
[figure not shown]
The Talar Convexity Angle (TCA) is formed by connecting the posterior talar tubercle (**a**), the most proximal part of the talus (**b**), and the deepest point of the transition to the talar neck (**c**)

Secondly, (12) age, (13) sex, (14) height, (15) BMI and (16) sports intensity (by means of the Ankle Activity Index (AAI)) will be implemented in the model as important patient characteristics, in case of a significant correlation. All these variables have shown a (prospective or retrospective) correlation with ankle instability in previous research apart from MDTA, MMHA and TCA. These three, however, have shown a relation with other pathologies that also concern an inversion-plantarflexion trauma mechanism and will therefore be explored on a potential correlation with CAI [14, 16, 30].

To assess overall recovery and CAI at 12 months, a questionnaire including patient reported outcome measures (PROMs) will be used. This questionnaire includes the FAOS and CAIT. The FAOS is a Dutch validated questionnaire assessing pain, other symptoms (swelling, locking, mobility, stiffness), function (activities of daily living) and sports and foot- and ankle related quality of life divided over 5 subscales, with scores ranging from 0 to 100 [31, 32]. The CAIT is scale consisting of 9-items measuring the severity of functional ankle instability per ankle individually. The total score ranges from 0 to 30 with a cut-off value discriminating between a functionally stable and instable ankle of 11.5 points (as calculated for the Dutch population) [33, 34].

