#### PREDICT sample size

For a prognostic model at least 20 EPV is needed to optimize reliability and to avoid bias in regression coefficients [37–39]. Based on having maximally 16 variables with a minimum of 20 events per variable, a prevalence of 30–40% after an initial sprain, including a 10% loss-to-follow-up, a sample size of 1185 patients is needed to perform the internal and 1185 patients is needed to perform the external model validation, resulting in a total of 2370 patients (Table 2).

During the study the required sample size may change and will be recalculated accordingly in case one of the following scenarios occur:In case one or more radiographic factors have a low inter- or intra-observer reliability (ICC ≤0.70), they will be excluded from the risk assessment model and the sample size will be recalculated using the new number of prognostic factors. If radiographic assessments cannot be performed in more than 2 cases (> 5%) a candidate predictor will be excluded, as the problem is likely to recur and therefore cannot be adequately assessed, now and during future assessment (e.g. up to 5% missing data is accepted) [40, 41].In case of multicollinearity between (ICC > 0.70) between prognostic variables one will be excluded;If a variable lacks agreement (ICC ≤0.70) with CAI it will be excluded;In case the prevalence of CAI during the study differs from the estimated 30%. In case the percentage of patients progressing to CAI exceeds the 50%, the sample size calculation will be based on the number of non-events. The prevalence will be recalculated when 500, 750, 1000, 1250, 1500, 1750,2000 and 2250 patients have returned the last questionnaire to minimize patient burden, as inclusion will stop as soon as the minimal required sample size is reached.

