### Data analysis and statistics

Demographics of the study population will be analyzed using the descriptive statistics. All statistics will be performed with SPSS version 23.0 (SPSS Inc., Chicago, IL, USA) and R package ‘Stats’ version 3.3.3 (University of Auckland, Auckland, New Zealand). A *p*-value of < 0.05 is considered significant. Normality of data will be assessed using the Shapiro-Wilks test.

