#### Prognostic model

For internal validation a maximal amount of data is required to increase the reliability, therefore apparent validation will be used, including the full sample size of 1026 patients. To increase reliability the bootstrapping procedure will be used in the development of the model. A sample of 1000 bootstraps will be used to assess bias in the regression coefficients. Additionally the sensitivity, specificity and ROC curve will be used to assess the predictive value of the model.

To define generalizability of the created model, temporal validation is chosen to decide whether patients will be included in the internal or external validation database. After determining the prognostic value of the included variables, the full required sample size is calculated. Additionally the duration until this sample size will be reached, is estimated. Subsequently the time stamp for the temporal validation is decided. This ensures both sample sizes will be sufficient and reached. Again the sensitivity, specificity and ROC curve will be used to assess the suitability of the model [36].

Variables with a significant correlation with CAI (age, sex, height, BMI, sports intensity, varus/valgus alignment, fibular position, tibiotalar contact ratio, height medial malleolus and talar convexity), in addition to a continuous model, will be categorized to provide a binary model that can be easily implemented in daily practice by simply answering question by ‘yes’ or ‘no’. For this the Youden index and a ROC curve will be used [33]. For both models the final objective is to create a model with cut-off values that advises surgery, watchful waiting or no surgical treatment by combining the scores with the patients expectations in the shared decision making process.

The cut-off values will be reflected to the MDC, SEM and MCID to ensure minimal measurement bias.

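### The recovery analysis lets a normality test choose between mean/SD and median/range; at the planned size that choice will largely reflect sample size, and neither option gives the within-patient change with its precision

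*Protocol article*

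**What the plan says.** Under Data analysis and statistics, one normality test is named for the whole study: "Normality of data will be assessed using the Shapiro-Wilks test". The significance level there is a p-value "of < 0.05 is considered significant". No other criterion for normality is given.

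Under Additional analyses in the same part, the default for recovery is that "mean and Standard Deviation (SD) of the functional outcome scores are calculated using the paired T-test". The alternative is: "In case of skewed data the Wilcoxon signed rank test will be used instead, reporting the median and range".

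Clinical outcome measures describes the scores. The FAOS has five subscales, "with scores ranging from 0 to 100". For the CAIT, "The total score ranges from 0 to 30 with a cut-off value" that separates stable from unstable ankles.

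On size, PREDICT sample size states that "a sample size of 1185 patients is needed to perform the internal" validation, with as many again for the external one (2370 in total). The Prognostic model paragraph under Data analysis and statistics works with a different figure, "including the full sample size of 1026 patients". Only the 12-month questionnaire is mandatory (Study design). Table 1 asks in addition for any one of the three earlier ones.

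**The concern.** A normality test answers whether a departure from normality can be detected, and with enough patients almost any departure can. FAOS and CAIT scores are bounded and move in steps, so they are not exactly normal to begin with. At the planned numbers the result of the test therefore says little about whether a mean change can be used. A paired mean change from several hundred or more patients has a sound confidence interval even when the scores are visibly non-normal.

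The switch leads to a weaker summary. The range depends on the two most extreme patients and widens towards the scale limits as the cohort grows. The first Additional analyses section, under Analyses, gives the purpose as judging recovery by comparing scores over time. The natural result is how much patients change and how precisely that is known. Both branches describe the scores at each time point and add a test; neither names the paired change or an interval for it.

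**Working it through.** **1. The size on which the argument rests.** Events = 20 per variable × 16 variables = 320. At 30% prevalence, 320 / 0.30 = 1066.7 evaluable patients. With 10% loss, 1066.7 / 0.9 = 1185.2, which reproduces the stated 1185. (With the table's rounded factor, 320 × 3.33 / 0.9 = 1184.) For the prognostic-value stage, 160 / 0.30 / 0.9 = 592.6, stated as 593, or about 533 evaluable. The figure of 1026 does not follow from 16 variables; 14 × 20 / 0.30 × 1.10 = 1026.7 would give it. For this point the difference is immaterial, since either figure is about 1000.

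**2. Assumptions.** The article gives scale limits but no means, SDs or correlations for the two scores. Scores were simulated as correlated normal values, rounded to a grid and cut off at the scale limits:
- FAOS-like: first measurement mean 50 to 55 (SD 12 to 20), 12 months mean 55 to 82 (SD 12 to 25), steps of 1.47 to 6.25 points.
- CAIT-like: mean 12 to 15, then 16 to 20 (SD 4 to 7), steps of 1 point.
- Correlation 0.4 to 0.5; Shapiro-Wilk at 0.05; 400 runs per setting.

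**3. How often Shapiro-Wilk rejects.**

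| Tested quantity | n = 300 | n = 1026 to 1066 |
|---|---|---|
| 12-month scores | 9 to 100% | 100%, except about 40% in the most favourable setting (no ceiling, fine grid) |
| First-measurement scores | 9 to 100% | 100% in most settings; lowest 16% |
| Paired differences | 8 to 82% | 23 to 100% |

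At the larger size the skewness of the differences lay between -0.13 and 0.

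**4. What the test responds to.** Take a symmetric FAOS-like score with no ceiling (means 50 and 55, SD 12). On a 2.78-point grid the differences are rejected in about 45% of runs at n = 300 and in 100% at n = 1066. On a 1.47-point grid the figures are about 10% and 40%. Skewness is zero throughout. Only the number of patients and the step size have changed.

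**5. Whether the mean change needs protecting.** At n = 1026 to 1066 the ordinary 95% t interval for the mean paired change covered the true value in 92.5 to 96% of runs across all settings. The switch guards against a problem that is not present.

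**6. What the fallback shows.** At these sizes the sample range covered 78 to 100% of the scale at the first measurement and 74 to 100% at 12 months. The 12-month interquartile range covered 16 to 34%. The difference between the two medians lay within about 1.4 points of the mean change (for example 26.9 against 25.6 for a FAOS-like score, and 8.0 against 7.7 for a CAIT-like one).

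**7. One example.** CAIT-like integers, assumed means 20 then 23, SD 6, correlation 0.5, n = 1066. Scores and differences were both rejected in 100% of runs, with skewness of the differences about 0. The plan would report roughly 20 (1 to 30) and 23 (4 to 30). The same data give interquartile ranges of 16 to 24 and 19 to 27, and a mean change of about 2.8 with a half-width of 0.34 (1.96 × SD of the differences / √n, with SD about 5.65: 1.96 × 5.65 / 32.65 = 0.34). With the same inputs, the differences are rejected in only about 20% of runs at n = 300, about 55% at n = 533 and 88% at n = 746.

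**The case against.** Four points can fairly be made against this.

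First, the trigger is inferred. The fallback is tied to skewed data, whereas Shapiro-Wilk detects any non-normality, and no sentence says that its p-value alone decides. This stands. The link is still the natural reading, because no other criterion is named.

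Second, a reader might infer that the t-test branch can never be used. The documents do not support that. A paired t-test concerns the differences, and the article does not say whether scores or differences are tested. Nor is 1000 the number of pairs: with only the 12-month form and one earlier form required, a given comparison may have far fewer. At n = 300 the differences were rejected in as few as 8% of runs.

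Third, a reader might infer that the fallback conveys no size of recovery at all, or that a ceiling would hide the change in medians. Neither follows. Subtracting the medians gives a crude size, close to the mean change in every setting tried. A near-perfect median about two weeks after a sprain that the article itself regards as severe has no basis in the text.

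Fourth, an article may leave confidence intervals and quartiles to a fuller plan, and Wilcoxon with medians is not an error for bounded scores. The absence of an interval would not carry the point alone. But the article does fix a switch and does name the range as the summary, and both are open to comment as written.

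**Conclusion.** The point holds as a minor improvement. If the Shapiro-Wilk result drives the switch, then with several hundred to about 1000 or more patients it will very likely trigger on the scores and often on the paired differences, mainly because of sample size. The rate depends on how many pairs are complete, how coarse the score steps are, and whether scores or differences are tested; the article leaves the last of these open. In the fallback the range takes up roughly three quarters to all of the scale. Neither branch names the within-patient change or its precision.

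All rejection rates and ranges rest on assumed score distributions. Recovery is an additional analysis: the risk model, its sample size, the choice of predictors and the cut-offs do not depend on it.

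**What to change.** In Additional analyses under Data analysis and statistics, replace the conditional rule for recovery:
- For the CAIT and each FAOS subscale, report the mean paired change between the named time points with a 95% confidence interval (bootstrap if preferred) and the number of complete pairs, whatever a normality test gives.
- Wherever a median is shown, give the interquartile range with it instead of the range.
- Keep the Wilcoxon signed rank test as a sensitivity analysis.

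If a normality check is retained for description, state whether it is applied to the scores or to the paired differences. The cost is a change of wording: same data, same software and no additional patients.
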